### SAMPLE SIZE

According to our data, approximately 78% of women will start their labor spontaneously before 41 weeks, meaning that 22% will have an induction of labor for medical reasons other than gestational age. Hence, considering 10 events (spontaneous onset of labor) for each of these 15 variables, and doubling this quantity for the elaboration of two different models, 13 participants will be required for each of these variables, hence 390 women are needed. Assuming a 10% rate of women with missing values in at least one predictor, 429 **patients** are needed.

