## 4 STATISTICS AND METHODOLOGY

### 4.1. Statistical analysis plan

#### MAIN ANALYSIS

The main outcome (spontaneous onset of labor vs. induction of labor between 41 and 42 weeks of pregnancy due to gestational age) will define two groups. The distribution of continuous or categorical variables among the units will be compared using Student's T test or Fischer's exact test, respectively. Two-sided significance level was set to 0.05.

A model of prediction of the binary outcome will be elaborated using stepwise backward and forward logistic regression analysis, including all analyzed features (gestational age at data collection will be included as an independent variable). To add or remove variables from the model, p-values of 0.05 or 0.10 will be used, respectively. Goodness-of-fit of the model will be evaluated using Hosmer and Lemeshow test and, if multiple models are achieved, the best one will be selected searching parsimony and following Akaike's Information Criterion. Area under the Receiver-Operating Characteristics curve will be used to assess predictive ability of the model. This value will be also calculated using bootstrapping resampling methods (1000 repetitions) to internally validate the results. As only a subset of the sample will have the measurement of cervical stiffness using Pregnotia device (as this assessment was lately introduced), a secondary analysis (following the same principles of the main analysis) will be performed. A correlation analysis will be carried out comparing cervical consistency index evaluated by ultrasound with cervical stiffness assessed using the aspiration device, as both measurement evaluate the same biophysical characteristic of the cervix.

The probability of spontaneous onset of labor for each day after the analysis will be evaluated using survival regression models. The data will be described using Kaplan-Meier's non-parametrical survival function and the predictive model will be estimated using stepwise backward and forward Cox's regression (proportional hazards model). As mentioned before, data regarding women whose labors have been induced due to maternal or fetal indication (different from gestational age) or with prelabor rupture of membrane without spontaneous onset of labor after 12 hours of expectant management will be censored at the time of admission for these causes.

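### Student's t test on two very unequal outcome groups holds the stated 0.05 level only if the group SDs are equal; naming Welch's test is a minor, free improvement to the univariate comparisons

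*Protocol*

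**What the plan says.** Protocol section 4.1, Main analysis, forms two groups from the main outcome: "spontaneous onset of labor vs. induction of labor between 41 and 42 weeks of pregnancy due to gestational age". Continuous and categorical features "will be compared using Student's T test or Fischer's exact test, respectively". The level is fixed in the next sentence: "Two-sided significance level was set to 0.05". The protocol gives no unequal-variance version, variance check or rank-based alternative.

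The only information on group sizes is in the sample size paragraph of section 3.1: "approximately 78% of women will start their labor spontaneously before 41 weeks". The remainder is described there as follows: "22% will have an induction of labor for medical reasons other than gestational age".

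The predictor table in section 2.2 includes fetal fibronectin as a concentration in ng/mL, and the Bishop score.

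**The concern.** The pooled t test estimates one common variance, and the larger group dominates that estimate. With groups of similar size this does little harm even if the spreads differ. With very unequal groups, the standard error is wrong whenever the spreads differ. It is too large if the smaller group is the less variable one, and too small if the smaller group is the more variable one.

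What is at stake is the set of feature-by-feature p-values, and any statement in the report that a feature does or does not differ between women who labor spontaneously and women induced for gestational age. The cervical stiffness analysis is to follow the same principles in a subset, so it inherits the choice with smaller groups.

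**Working it through.** **The plan's own figure first.** Inputs are in section 3.1: "considering 10 events (spontaneous onset of labor) for each of these 15 variables", "doubling this quantity for the elaboration of two different models", and 10% for missing predictors.

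- 10 / 0.78 = 12.8, rounded up to 13 women per variable.
- 13 × 15 × 2 = 390.
- 390 × 1.10 = 429.

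The figure reproduces exactly. It is an events-per-variable rule and does not involve the t test.

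**Group imbalance.** If 78% have spontaneous onset before 41 weeks, the gestational-age induction group can be at most 22%, and 78 / 22 = 3.5. Two things push the ratio higher. The endpoint table in section 2.2 counts spontaneous onset up to 41 3/7 weeks, and section 3.1 attributes the 22% to inductions for other reasons, which belong to neither outcome group. Two splits are used below:

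- 335:94, which is 0.78 × 429 = 335 and the rest, a bound favorable to the plan.
- 351:39, an assumed 90:10 split of 390.

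**Formula.** Let n1 be the larger group with SD 1, n2 the smaller group, and r the SD ratio (smaller over larger). The documents do not give r; the range 0.5 to 2 is an assumption.

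- Pooled variance: s² = [(n1 − 1) + (n2 − 1)r²] / (n1 + n2 − 2)
- Variance used by Student's test: VS = s²(1/n1 + 1/n2)
- True variance of the mean difference: V = 1/n1 + r²/n2
- True level ≈ 2[1 − Φ(t × √(VS/V))], with t the 97.5% point on n1 + n2 − 2 degrees of freedom

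**Worked cases.**

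- 335:94, r = 2: s² = (334 + 93 × 4)/427 = 1.653; VS = 0.0225; V = 0.0455; √(VS/V) = 0.703; 1.966 × 0.703 = 1.382; level 16.7%.
- 335:94, r = 0.5: s² = (334 + 93 × 0.25)/427 = 0.837; VS = 0.01140; V = 0.00564; √(VS/V) = 1.421; 1.966 × 1.421 = 2.793; level 0.5%.
- 351:39, r = 2: s² = (350 + 38 × 4)/388 = 1.294; VS = 0.0369; V = 0.1054; √(VS/V) = 0.591; 1.966 × 0.591 = 1.163; level 24.5%.

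**Simulation check** (normal data, equal means, 40,000 runs per cell):

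| SD ratio | Student 335:94 | Student 351:39 | Student 195:195 | Welch 335:94 | Welch 351:39 |
|---|---|---|---|---|---|
| 0.5 | 0.5% | 0.1% | 5.0% | 4.9% | 5.0% |
| 0.67 | 1.4% | 0.7% | 5.0% | 5.0% | 5.0% |
| 0.8 | 2.6% | 1.9% | 5.4% | 5.0% | 4.9% |
| 1 | 4.9% | 4.9% | 5.0% | 4.9% | 4.8% |
| 1.25 | 8.4% | 10.0% | 5.0% | 5.0% | 5.1% |
| 1.5 | 11.5% | 15.3% | 5.0% | 5.0% | 4.9% |
| 2 | 17.0% | 24.7% | 5.2% | 4.9% | 5.0% |

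With equal groups the level stays near 5%, so it is the imbalance that makes unequal spread harmful.

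**Power.** Take 335:94, r = 0.67 and a true difference of 0.3 SD (SD of the larger group). V = 0.00776, so the standardized difference is 0.3/√0.00776 = 3.41, and √(VS/V) = 1.243.

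- Student: Φ(3.41 − 1.966 × 1.243) = 83%.
- Welch: Φ(3.41 − 1.97) = 92%.

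**The case against.** The case against has four parts.

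- **The variant is not written out.** The protocol does not say pooled, and the choice of variant could be left to a separate analysis plan. The first half is true. But the protocol names the test, and the name ordinarily means the equal-variance test, so this is a choice made and not a detail left open.
- **The inflation needs an unusual pattern.** The high error rates need equal means together with a more variable smaller group, and nothing in the documents suggests that for any feature. If spread follows the mean, equal means imply equal spread and Student's test holds its level. With identical lognormal groups (log-SD 1 to 1.5) it stays at about 5%. This stands. A smaller group with lower values and lower spread leads to lost power, not false positives.
- **Little depends on these tests.** The stepwise logistic model takes in all features, with no t-test screen. The primary objective concerns model performance, judged by AUC. The secondary objectives concern accuracy and daily probability of onset, not mean differences. This stands and limits the point to a minor one.
- **The alternatives are imperfect.** In the same lognormal null case Welch's test rejects in about 6% to 13%. The rank-sum test at 335:94 rejects in about 2% to 10% for SD ratios of 0.5 to 2. This also stands: neither test suits every feature, and choosing after seeing how skewed the data are adds another loose end.

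**Conclusion.** The point holds as a minor one. The named test holds its stated 0.05 level in these groups only under equal SDs, and the protocol gives no ground for assuming that. The tabulated levels rest on assumed SD ratios, normal data and two illustrative splits.

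Three stronger readings are tempting, and the documents support none of them:

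- **That false-positive rates of 17% to 25% are to be expected.** These are the ends of an assumed range. No SD by group is given, and the direction of any difference is unknown.
- **That 335:94 is the plan's own comparison.** The 22% is described as induction for other reasons, so the split serves only as a bound. The true imbalance is probably larger, but its size is not stated.
- **That the prediction models or the sample size are compromised.** The t tests feed neither of them, nor the AUC. The effect stops at the univariate comparisons and the statements based on them.

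**What to change.** In section 4.1, Main analysis:

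- Replace Student's t test with Welch's unequal-variance t test for roughly symmetric continuous features, and report the mean difference with its Welch 95% interval.
- List in advance the features to be compared by the Wilcoxon rank-sum test, namely fetal fibronectin and Bishop score. State that the result is read as a comparison of distributions, not of means. Log-transforming fibronectin is an acceptable alternative if it is fixed beforehand.
- Do not let observed skewness decide which test is used.

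The cost is a sentence or two of wording. No further data or recruitment is needed, and nothing changes in the models or the sample size. The change does not guarantee an exact 5% level for every feature, but it removes the dependence on equal SDs for the features tested by Welch's method.

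### The stepwise rule (entry 0.05, removal 0.10, 15 candidates) keeps at least one noise variable in roughly half to four fifths of datasets, and the bootstrap as described need not remove the resulting optimism in the ROC area

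*Protocol*

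**What the plan says.** Under Main analysis in section 4.1, the logistic model is to be "elaborated using stepwise backward and forward logistic regression analysis, including all analyzed features", with gestational age at data collection among the covariates. The thresholds are explicit: "To add or remove variables from the model, p-values of 0.05 or 0.10 will be used, respectively". If several models result, parsimony and AIC decide between them. Predictive ability is judged by the area under the ROC curve, which is also to be calculated with 1000 bootstrap repetitions as internal validation. The text does not say whether selection starts from the full or the empty model, whether it is repeated in each bootstrap sample, or whether optimism is subtracted.

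The Cox model for the second main outcome is also selected stepwise in both directions. For that model the section names neither a discrimination measure nor a bootstrap.

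The sample size section in 3.1 fixes the number of candidates: "considering 10 events (spontaneous onset of labor) for each of these 15 variables". The predictor table in section 2.2 also lists 15.

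**The concern.** The rule tests many candidates one at a time at 0.05 or 0.10, and no overall test stands in front of it. It will therefore often name variables that carry no information. Which variables matter is part of what the study wants to learn: the primary objective concerns the performance of different features in predictive models, and secondary objectives 2 and 5 ask for the influence of each variable. The Background says that fetal fibronectin failed to discriminate in earlier work and that Placental Alpha Microglobulin-1 has not been evaluated for term labour. A reader will want those two confirmed or rejected, and a nominal p-value after stepwise selection cannot do that.

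Selection also inflates the ROC area calculated on the same data. The bootstrap is the plan's only safeguard against this, and it works only if the whole selection is repeated in each resample.

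**Working it through.** **Inputs from the protocol.** Entry 0.05 and removal 0.10 (4.1); 15 candidates and 390 women analysed (3.1, Sample size); "approximately 78% of women will start their labor spontaneously before 41 weeks" (same place).

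**The plan's own figure.** 10/0.78 = 12.8, rounded up to 13 per variable; 13 × 15 × 2 = 390; 390 × 1.10 = 429. Both stated totals are reproduced. The protocol gives no false-selection rate.

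**No candidate predictive, candidates independent.** P(at least one retained) is about 1 − (1 − threshold)^k:

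| Candidates k | Forward, 0.05 | Backward, 0.10 |
|---|---|---|
| 14 | 51.2% | 77.1% |
| 15 | 1 − 0.95^15 = 53.7% | 1 − 0.90^15 = 79.4% |
| 16 | 56.0% | 81.5% |

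The rows for 14 and 16 are there because cervical stiffness goes to a secondary analysis and gestational age at collection is added.

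**Simulation check (logistic, N = 390, 15 candidates, 500 null datasets per setting).** With a 22% minority outcome and independent candidates: backward 78.8%, forward 52.6%, lower-AIC model of the two 78.8%. The Monte Carlo standard error near 79% is √(0.79 × 0.21/500) ≈ 1.8 points. Assumed correlations (0.3 or 0.5 throughout, or a correlated cervical block) gave backward 79–85% and forward 36–49%. An assumed 10% minority outcome gave 82% and 55%. A smaller Cox run (200 null datasets, 78% events) gave 80% backward.

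**Two true predictors assumed.** This leaves 13 noise candidates: forward 1 − 0.95^13 = 48.7%, backward 1 − 0.90^13 = 74.6%. Backward is expected to keep about 13 × 0.10 = 1.3 noise variables.

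**Effect on the ROC area.** At 22% minority, backward-selected null models had a mean apparent area of about 0.60 (5th–95th percentile 0.56–0.65); at 10% minority the mean was 0.63. For the bootstrap, 80 null datasets that yielded a backward model were each resampled 100 times:

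| Quantity | Mean ROC area |
|---|---|
| Apparent | 0.597 |
| Final model simply resampled | 0.597 |
| Optimism-corrected, terms held fixed | 0.586 |
| Optimism-corrected, selection repeated | 0.521 |

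**Overall test.** A likelihood-ratio test of the full 15-predictor logistic model was significant at 0.05 in about 4% to 7.5% of null datasets across runs.

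**The case against.** The strongest reply is that the protocol never treats obtaining a model as the answer to its primary question. It asks about performance and measures it by ROC area with bootstrap validation, alongside a goodness-of-fit test. A reader might infer from the 79% that the study cannot tell a useful predictor set from a useless one. The documents do not support that: a bootstrap with selection repeated brings the null area close to 0.5 and would expose a useless set. What remains is that 4.1 does not say selection is repeated, and for the Cox model it specifies no such check.

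Second, a null in which nothing predicts is unlikely here, because the Background reports that cervical length and body mass index were associated with spontaneous onset. This is fair, and the 54–79% range is conditional on that null. The two-predictor calculation shows that the problem persists without it.

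Third, a reader might infer that the plan breaks its own error rate, since it says "Two-sided significance level was set to 0.05". That sentence closes the paragraph on the t-test and exact-test group comparisons. The selection thresholds are stated separately and openly, so no overall 0.05 is promised for the models.

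Fourth, the secondary analysis by gestational age names logistic and survival analyses but does not say that they use stepwise selection. The repetition of the search there is not established. The stiffness analysis does follow the principles of the main analysis.

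Finally, the starting model and bootstrap details may be settled in an analysis plan that is not at hand. The selection method and its thresholds, however, are fixed in the protocol itself.

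**Conclusion.** The point holds in a conditional form. With 15 independent candidates and none predictive, the rule retains at least one in about 54% (forward) to 79% (backward, or lower-AIC choice of both) of datasets. With two assumed true predictors, it keeps at least one noise variable in about 49% to 75%. An unconditional figure of 80% would be wrong: it needs a backward start or an AIC choice between directions, as well as a null that the Background makes unlikely.

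The apparent ROC area of a backward-selected null model is about 0.60, and the bootstrap as described leaves it there unless selection is repeated (0.597 against 0.521).

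The correlations, the two true predictors and the minority fractions are assumptions. The 22% is the complement of the protocol's 78%; the size of the group induced for gestational age is not given. The ROC figures come from the logistic model only.

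**What to change.** Amend section 4.1, for the logistic and the Cox model alike:

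1. Add one likelihood-ratio test of the full prespecified model against a model with gestational age at data collection only, at two-sided 0.05, as the overall test of association. It shows whether anything is associated with onset; usefulness for prediction still rests on discrimination.
2. Label the variables and p-values from stepwise selection as exploratory.
3. State the starting model, repeat the whole selection in each of the 1000 bootstrap samples, and report optimism-corrected discrimination: ROC area for the logistic model, a concordance index for Cox.

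Penalised estimation may be used for shrinkage, but should not be presented as a cure for naming noise variables. In a check with two assumed true predictors, cross-validated LASSO kept 2.5–2.9 noise variables against 1.2 for backward selection, with equal or slightly lower test ROC area and slightly lower test deviance.

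The cost is rewording and computing time, with no additional women or data. The downside is a somewhat lower reported ROC area and fewer predictors claimed as established.

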## 2 PROJECT OBJECTIVES AND DESIGN

### 2.1 Hypothesis, primary and secondary objectives

#### *Hypothesis*

The evaluation of different clinical features, together with the ultrasonographic assessment of local cervical conditions and the estimated fetal weight, combined with the biochemical determination of fetal Fibronectin and Placental Alpha Microglobulin-1 in vaginal secretions will provide the probability of spontaneous onset of labor during the remaining days of pregnancy, hence allowing the discrimination between those women who will spontaneously trigger their deliveries from those who will require an induction of labor.

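### The only fit check for the logistic prediction model, a Hosmer-Lemeshow test on the data that built it, cannot detect overfitting, and the planned bootstrap covers only the ROC area

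*Protocol*

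**What the plan says.** Protocol section 4.1 (Main analysis) builds the binary model with selection driven by p-values: it "will be elaborated using stepwise backward and forward logistic regression analysis, including all analyzed features", and "To add or remove variables from the model, p-values of 0.05 or 0.10 will be used, respectively". It then gives each assessment its own tool:

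- **Fit:** "Goodness-of-fit of the model will be evaluated using Hosmer and Lemeshow test".
- **Choice between competing models:** parsimony and Akaike's criterion.
- **Discrimination:** "Area under the Receiver-Operating Characteristics curve will be used to assess predictive ability of the model".
- **Internal validation:** "This value will be also calculated using bootstrapping resampling methods (1000 repetitions) to internally validate the results". The value meant is the ROC area named in the sentence before.

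The section mentions no calibration plot, slope or intercept, and no split or external sample. The cervical-stiffness analysis follows the same principles, and the analyses stratified by gestational age also use logistic regression.

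Section 2.1 states the aim as a probability: the predictors "will provide the probability of spontaneous onset of labor during the remaining days of pregnancy". The primary objective is also worded around the probability of spontaneous onset.

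**The concern.** A model meant to state a probability must be calibrated: among women given 80%, about 80% should go into labor spontaneously. The ROC area depends only on ranking and cannot show this. The design is exposed to overfitting, with 15 candidate variables, stepwise selection and a limited number of women in the smaller outcome group. Overfitting makes predictions too extreme in new women. The one check given to fit is run on the data that produced the model, where this error cannot be seen. Followed as written, section 4.1 could report a non-significant fit test and a good ROC area for a model whose probabilities are materially wrong, and nothing in the planned output would show it.

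**Working it through.** **1. The protocol's sample size.** It is based on "considering 10 events (spontaneous onset of labor) for each of these 15 variables, and doubling this quantity for the elaboration of two different models" and a 78% event rate. 10 / 0.78 = 12.8, rounded up to 13 women per variable. 13 x 15 x 2 = 390, and 390 x 1.10 = 429. The figures reproduce.

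**2. Women in the logistic contrast.** The contrast is spontaneous onset against induction for gestational age. Inductions for other indications are censored (section 2.2), and the sample-size text puts them at 22%. If they leave the contrast, 390 x 0.78 = 304, so about 300 to 390 women is the relevant range. The minority share within the contrast is not given. It is assumed here to be 10 to 22%.

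**3. Why the slope is 1 on the fitting data.** Let X be the selected variables with an intercept, b the maximum-likelihood estimate and p the fitted probabilities. The score equations give X'(y - p) = 0. Hence 1'(y - p) = 0 and (Xb)'(y - p) = 0. These are the score equations for regressing y on the linear predictor Xb, and they are solved by intercept 0 and slope 1. This holds however the variables were chosen and needs no simulation. A decile test on the same data can react only to what remains, such as curvature.

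**4. Size under assumptions.** The simulation used N = 390, 15 candidates with pairwise correlation 0.2, and entry and removal at 0.05 and 0.10. Hosmer-Lemeshow used 10 groups, 8 df and alpha 0.05. The slope was measured in 20,000 new women. Assumed log-odds per SD were 0.3, 0.3, 0.2, 0.2 (weak) or 0.6, 0.4, 0.3, 0.2 (moderate), with the other 11 null.

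| Effects | Minority share | Usable runs | Median slope, new women | Slope < 0.8 | Hosmer-Lemeshow non-significant among those | ROC area, fitted / new |
|---|---|---|---|---|---|---|
| Weak | 10% | 397 | 0.56 | 88% | 95.4% | 0.707 / 0.624 |
| Weak | 22% | 400 | 0.68 | 78% | 92.3% | 0.689 / 0.635 |
| Moderate | 10% | 400 | 0.69 | 75% | 96.3% | 0.775 / 0.704 |
| Moderate | 22% | 400 | 0.80 | 51% | 94.6% | 0.755 / 0.717 |

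Monte Carlo standard errors of the non-significance column are about 1.1 to 1.6 points. For example, the last row has 0.51 x 400 = 204 models, and sqrt(0.946 x 0.054 / 204) = 1.6 points. A separate simulation at N = 390 and 305 with the same range of shares gave 93 to 98%.

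**5. Extreme case.** With all 15 predictors pure noise (true slope 0, true ROC area 0.50; shares 5, 10 and 22%), stepwise models still gave a non-significant test in 94.1 to 95.4% of runs, with apparent ROC areas of 0.60 to 0.68.

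**6. The same models on other data.** For the four rows of the table, Hosmer-Lemeshow in new samples of equal size (10 df) was non-significant in 55 to 68%. Much of the blindness therefore comes from testing on the fitting data.

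**7. What a slope of 0.68 means.** Suppose 78% spontaneous onset, so the average logit is ln(0.78 / 0.22) = 1.27. A woman predicted one logit lower is given logit 0.27, or 57%. At slope 0.68 her logit is 1.27 - 0.68 = 0.59, or 64%. The gap is about 8 points before rounding (56.6% against 64.2%).

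**The case against.** **Detail for a statistical analysis plan.** Naming a conventional fit test is ordinary in a protocol, and a later plan could add calibration measures. That is fair as far as absence goes. But section 4.1 does make the choice: it gives fit to Hosmer-Lemeshow and limits the bootstrap to the ROC area. That choice needs correcting wherever the detail is written.

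**Validation was given to the bootstrap.** This is true, and a bootstrapped ROC area can show optimism in ranking. It does not show whether the stated probabilities are right. Replacing the test would not remove the overfitting either. It would only make it visible.

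**The hypothesis concerns daily probability.** Its wording fits the Cox model at least as well, where Hosmer-Lemeshow is not used, and it goes on to speak of discrimination. That weakens the hypothesis as sole support, but the primary objective also speaks of probability.

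Some stronger readings are tempting and are not supported:

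- *That the protocol accepts a model when p exceeds 0.05.* It states no such rule. The sentence "Two-sided significance level was set to 0.05" closes the paragraph on comparing the two groups and is not attached to the fit test.
- *That the test passes almost whatever the truth.* It keeps some power against a wrong functional form. With an omitted quadratic term, a simulation at N = 390 had it miss in 52 to 78% of runs at a 22% share and 67 to 86% at 10%, so it detected some. Those figures rest on invented curvature, and the protocol sets no miss rate to judge them by.
- *That 390 women and a 22% minority share describe the logistic analysis.* The 22% is the group induced for other indications, which is censored.

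**Conclusion.** The point holds for overfitting in the logistic model. It rests on two things in section 4.1, the sole fit check and a bootstrap restricted to the ROC area, together with an algebraic fact about maximum-likelihood fits. That the test is run on the development data is inferred, because no other data are described.

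The size is conditional. Effect sizes, correlations and the minority share are assumptions. Within them the median slope in new women is about 0.5 to 0.8. The test is non-significant in roughly 93 to 98% of models with a slope below 0.8 (92 to 96% in the tabulated runs). This is simply what a 5% test gives when it cannot see the fault. The range could move with other inputs; the blindness of the check would not. The remedy is to add a calibration assessment. The point does not invalidate the design or the ROC analysis.

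**What to change.** In section 4.1, extend the 1000 bootstrap repetitions to calibration. In each repetition, repeat the whole stepwise selection, fit the model, apply it to the original sample, and estimate the calibration slope and intercept there. The apparent slope is 1, so the optimism-corrected slope is 1 - (1 - mean slope in the original sample), which is that mean. Report the corrected slope and intercept with a calibration plot, and name these as the calibration assessment. Apply the same to the cervical-stiffness and gestational-age logistic models.

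Hosmer-Lemeshow may stay as a descriptive supplement, with a sentence saying that non-significance is not evidence of adequate calibration. Shrinking the published coefficients by the corrected slope is optional.

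The cost is a few sentences and a few lines of code inside a bootstrap already planned, with no new participants or data. The reported calibration will look less favourable.

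### The bootstrap validation of the AUC does not state that stepwise/AIC selection is repeated in each resample or that optimism is subtracted; read literally, selection optimism stays in the main performance result.

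*Protocol*

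**What the plan says.** All of this stands in Protocol section 4.1, Main analysis, unless stated otherwise.

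- Outcome, which splits the women for comparison (sentence cut short): "The main outcome (spontaneous onset of labor vs. induction of labor between 41 and 42 weeks of pregnancy due to gestational age) will define two".
- Model building: "A model of prediction of the binary outcome will be elaborated using stepwise backward and forward logistic regression analysis, including all analyzed features".
- Thresholds: "To add or remove variables from the model, p-values of 0.05 or 0.10 will be used, respectively".
- Second layer of selection: "if multiple models are achieved, the best one will be selected searching parsimony and following Akaike's Information Criterion".
- Fit: "Goodness-of-fit of the model will be evaluated using Hosmer and Lemeshow test".
- Performance: "Area under the Receiver-Operating Characteristics curve will be used to assess predictive ability of the model".
- Validation, in the next sentence: "This value will be also calculated using bootstrapping resampling methods (1000 repetitions) to internally validate the results".

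The cervical-stiffness subset is to be analyzed on the same principles. The Cox model is also built stepwise, and the paragraph describing it names no validation step. Section 2.1 makes the performance of the predictive models the primary objective, so the AUC is the main result.

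**The concern.** In the order the protocol gives, the value to be bootstrapped is the AUC of the model that came out of selection. If that model is held fixed and its AUC is recomputed on resamples of the same women, the bootstrap distribution centers on the apparent AUC. That describes sampling spread. It does not measure how much of the AUC arose because the data chose the predictors and fitted their coefficients. To measure that, each resample must repeat every data-driven step, and the resulting model must be tested outside the resample.

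The goodness-of-fit test does not fill the gap, because a Hosmer-Lemeshow test in the fitting data does not measure overfitting.

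At stake is a headline AUC labeled internally validated that still carries its optimism. The background section wants a tool for counseling individual women, so predicted probabilities that are too extreme would matter as well.

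**Working it through.** **The plan's own figure.** The protocol states no AUC, optimism or validation target. The only figure to reproduce is the sample size, which rests on "considering 10 events (spontaneous onset of labor) for each of these 15 variables, and doubling this quantity for the elaboration of two different models".

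- 10 / 0.78 = 12.8, rounded up to 13 women per variable.
- 15 × 2 × 13 = 390.
- 390 × 1.10 = 429.

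Both totals reproduce. They neither support nor refute the point, but they supply the 15 candidates and the 390 complete cases used below.

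**Inputs from the protocol.** 15 candidates; entry at 0.05 and removal at 0.10; N = 390.

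**Inputs assumed, because the protocol does not give them.** Share of the smaller outcome group: 22% or 10%. The 22% is only a convenient value: in the Sample size paragraph it describes inductions for reasons other than gestational age, which are not the comparison group. At N = 390 these shares mean 0.22 × 390 ≈ 86 or 0.10 × 390 = 39 women in the smaller group, that is 86/15 ≈ 5.7 or 39/15 = 2.6 per candidate. Signal: none, or three true predictors with log odds ratio 0.35 per SD. Pairwise predictor correlation: 0.2.

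**Method.** 160 simulated data sets per setting, 40 resamples each, and the true AUC taken from 20,000 new subjects. The optimism-corrected value is:

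corrected AUC = apparent AUC − mean over resamples of (AUC of the resample's model in the resample − AUC of that model in the original sample).

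| Setting | Apparent | Bootstrap, model fixed | Bootstrap, selected variables refitted | Corrected, variables fixed | Corrected, selection repeated | True |
|---|---|---|---|---|---|---|
| N 390, 22%, signal | 0.696 | 0.696 | 0.701 | 0.686 | 0.650 | 0.660 |
| N 390, 10%, signal | 0.701 | 0.701 | 0.706 | 0.691 | 0.632 | 0.637 |
| N 390, 22%, no signal | 0.539 | 0.538 | 0.539 | 0.537 | 0.474 | 0.500 |
| N 390, 10%, no signal | 0.562 | 0.561 | 0.563 | 0.558 | 0.477 | 0.500 |
| N 195, 22%, signal | 0.707 | 0.708 | 0.714 | 0.694 | 0.629 | 0.629 |

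**Optimism left by the literal reading (fixed-model bootstrap minus truth), N = 390.**

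- Signal, 22%: 0.696 − 0.660 = 0.036.
- Signal, 10%: 0.701 − 0.637 = 0.064.
- No signal, 22%: 0.538 − 0.500 = 0.038.
- No signal, 10%: 0.561 − 0.500 = 0.061.

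The standard deviation of apparent minus true AUC across data sets was 0.035 and 0.048 in the two signal settings. The Monte Carlo standard errors of the mean gap are therefore 0.035/√160 ≈ 0.003 and 0.048/√160 ≈ 0.004.

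**Second simulation, different assumptions.** Independent candidates, four true ones with log odds ratios 0.5, 0.4, 0.3 and 0.2 per SD, N = 390, 60 runs.

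- 22%: fixed-model bootstrap 0.703 against true 0.660, a gap of 0.043; calibration slope 0.74; corrected with selection repeated 0.651.
- 10%: 0.728 against 0.639, a gap of 0.089; calibration slope 0.59; corrected 0.650.

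The gaps at N = 390 thus run from about 0.04 to 0.09. The upper end rests on only 60 runs. Neither simulation includes the further choice on AIC.

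**More generous readings.** Refitting the selected variables in each resample moves the value slightly up (0.701 against 0.696). A formal optimism correction with the variable set held fixed removes only 0.696 − 0.686 = 0.010 of the 0.036 gap. Only repeating selection brings the estimate near the truth when there is signal: 0.650 against 0.660, and 0.632 against 0.637.

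**The case against.** The strongest reply is that the protocol is silent, not wrong. It names the purpose as internal validation, which fits a bootstrap that repeats selection and corrects for optimism; the resampling algorithm may be set out in a separate SAP that is not at hand. In part this stands. A reader might infer that the protocol fixes a single run of selection and will certainly report an inflated AUC. The text does not say that, since repeating selection is nowhere excluded. But section 4.1 is itself headed as the statistical analysis plan and already fixes the p-values, the selection criterion, the number of resamples and the software. Having gone that far, it describes the validation in words that, followed as written, do not validate.

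Three further inferences would go too far:

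- That 22% is the size of the comparison group. It is not, and that size is not given. Nor need 390 be the number entering the logistic model, because women induced for other reasons fall in neither outcome group.
- That the stiffness subset is capped at 240 women or has some particular size. Section 8 says 240 probes are supplied free and states no cap. The N = 195 row only shows that optimism grows in smaller samples.
- That the corrected bootstrap is always within about 0.01 of the truth. With no signal it over-corrects, by 0.500 − 0.474 = 0.026 and 0.500 − 0.477 = 0.023.

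The simulated signal strengths and correlations are also assumptions, and several cervical measurements here are plausibly more strongly correlated. This affects the size of the optimism; in every setting tried, the fixed-model bootstrap stayed at the apparent value and above the truth.

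**Conclusion.** The point holds as a defect of specification with a predictable direction. The protocol does not state that selection is repeated within each resample or that an optimism-corrected AUC is reported. Carried out literally, the bootstrap returns the apparent AUC, and selection optimism stays in the primary performance result. Its size is illustrative: about 0.04 to 0.09 of AUC at N = 390 with 15 candidates, conditional on the assumed signal, predictor correlation and smaller-group share. That no such repetition is intended is not shown. This should be corrected before analysis; it does not call the data collection or the sample size into question.

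**What to change.** Replace the validation sentence in section 4.1 with an explicit procedure:

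1. In each of the 1000 resamples, repeat the full selection by a pre-set automated rule: stepwise with 0.05 and 0.10, then lowest AIC if several models result. The present appeal to parsimony is a judgment and must become a rule before it can be repeated.
2. Apply each resample's model to the original sample and take the difference in AUC as that resample's optimism.
3. Subtract the mean optimism from the apparent AUC and report the result as the internally validated AUC, with the optimism-corrected calibration slope alongside.
4. Do the same for the stepwise Cox model, using the C-index, and for the cervical-stiffness subset analysis.

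Shrinking the coefficients, or adding stiffness as a single term to the main model, are optional extras and not part of this change.

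Cost: more code and computing time, a lower reported AUC, and slight over-correction if the predictors carry no signal (about 0.475 against 0.500). No additional women, visits or measurements are needed. If the investigators already intend this procedure, the change only writes it down.
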